**Contact with patient**								
	**Visit 1**	**Visit 2**						**Visit 3**
	**0**	**Pre-biopsy**	**Biopsy procedure**	**1-min post-biopsy**	**1-h post-biopsy**	**6 h post-biopsy**	**24 h post-biopsy**	**2 weeks post-biopsy**
Consent	×							
Screening	×							
Baseline characteristic	×							
PSA	×							
MRI	×							
Randomisation	×							
Perineal nerve block (Perineal nerve block arm)		×						
Periprostatic block (Periprostatic block arm)		×						
Transperineal prostate biopsy (12-core systematic biopsy with/without cognitive targeted biopsy)			×					
Blood presure measurement		×	×	×				
Heart rate measurement		×	×	×				
Breath rate measurement		×	×	×				
External manifestations assessment			×					
NRS pain score assessment				×	×	×	×	
Anaesthesia satisfaction assessment							×	
Pathological assessment								×
Withdrawal	Complete as required at any time following registration							
SAE	Complete as required at any time following registration							

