▸ Post-biopsy pain severity score, for which pain will be evaluated by the NRS at 1, 6, and 24 h after the prostate biopsy.▸ Changes in blood pressure, heart rate and breathing rate during the biopsy procedure, which will be measured and recorded by a multi-parameter monitor from 1 min prior to anaesthesia (initial value) to 1 min after the prostate biopsy. The change will be defined as the difference between the average value during the anaesthesia and biopsy procedures and the initial value. Additionally, the difference between the maximum value and the initial value will be assessed.▸ External manifestations of pain during biopsy, which will be assessed by a research nurse who will be blinded to the block arm during the biopsy procedure. The pain assessment will be divided into five parts: the degree of facial expression (0 points for no particular expression or smile; 1 point for an occasional grimace or frown, a withdrawn expression, or a disinterested expression, 2 points for frequent or constant quivering chin or a clenched jaw), the degree of activity (0 points for lying quietly or being in a normal position, 1 point for slight contractions of the hip muscles or slight movements of hip, 2 points for severe contractions of the hip or lifting the hip out of the bed), the degree of voice expression (0 points for quiet or normal communication, 1 point for an occasional moan or weeping sound, 2 points for constant moaning or sobbing and screaming), the degree of pacification (0 points for being peaceful and not requiring pacification, 1 point for being able to be comforted easily, 2 points for being difficult to comfort) and the degree of cooperation (0 points for being calm and cooperative, 1 point for language resistance, 2 points for body resistance).▸ Anaesthesia satisfaction, or patient satisfaction with overall anaesthesia, which will be measured by a questionnaire at 24 h after the biopsy. Five items will be included to evaluate satisfaction: whether the pain during the biopsy was less severe than expected (scores from 0 to 10, where 0 represents far less severe, and 10 represents far more severe than expected); whether the pain after anaesthesia was less severe than the pain during anaesthesia (scores from 0 to 10, where 0 represents far less severe and 10 represent far more severe); weather the patient is satisfied with the overall feeling of the biopsy (scores from 0 to 10, where 0 represents the highest level of satisfaction, and 10 represents the lowest level of satisfaction); whether the patient would recommend this type of biopsy to other patients (scores from 0 to 10, where 0 represents they would highly recommend, and 10 represents they would definitely not recommend it); and whether the patient would still want to choose this way if they have to undergo another biopsy (scores 0 to 10, where 0 represents very willing to choose it and 10 represents extreme reluctance).▸ The detection rate for prostate cancer, defined as the proportion of men with prostate cancer among those who undergo a prostate biopsy.▸ The detection rate for clinically significant prostate cancer, defined as the proportion of men with prostate cancer of International Society of Urological Pathology (ISUP) grade 2 or higher, according to the 2014 ISUP classification, among men who undergo a prostate biopsy.▸ Adverse events, which will be recorded 7 days after this trial. These events mainly include haematuria, vagal reflex, infection, urinary retention and other adverse events identified by the Common Terminology Criteria for Adverse Events (CTCAE).

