### Randomisation

The participants who meet the criteria and sign the consent form will be allocated at a ratio of 1:1 to the perineal nerve block arm or periprostatic block arm by using block randomisation. The random sequence will be generated by the PROC PLAN statement of the SAS program and then sealed in envelopes. The randomised number will be known and kept by one research nurse and blinded to the others. The randomised number will be revealed to the urologist (the one who will perform anaesthesia) only when the participant has already entered the operation room for anaesthesia and the prostate biopsy.

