### Prostate Biopsy

Another urologist who is blinded to the block method will perform the prostate biopsy. All patients will undergo a 12-core systematic transperineal prostate biopsy with or without a targeted biopsy. The 12-core systematic biopsy region will be taken as described previously (14). A targeted biopsy will be performed using the cognitive fusion method (15), only when there is at least one suspicious lesion [defined as a lesion with a score ≥3 according to the Prostate Imaging Reporting and Data System (PI-RADS) criteria (16)] shown by the MRI. Another research nurse who is also blinded to allocation will record the manifestations of the patients during the biopsy procedure.

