### Statistical Analysis

The primary outcome in this trial will be analysed following the intention-to-treat principle as well as the per-protocol principle. The difference between the two groups will be evaluated with a 95% confidence interval (CI) using a generalised linear mixed model to express the precision of the estimate. In this model, the NRS pain score and the group will be considered the dependent variable, the imbalanced baseline characteristic will be considered the covariate, and the centre will be considered a random effect.

The secondary outcomes will be analysed with Pearson chi-square tests and expressed with 95% CIs. Each *P*-value reported in this trial will be two-sided.

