### Data Collection and Monitoring

After informed consent is obtained from the patients, the data will be collected by a research nurse who is blinded to the allocation to ensure the integrity of evaluation and prevent bias. Demographic information, including age, body mass index (BMI), PSA level, DRE results, prostate volume and American Society of Anesthesiologists (ASA) classification will be collected before anaesthesia. The pain score will be measured and recorded *via* form 1 (Figure 4) at 10 min, 1, 6, and 24 h after the biopsy. Additionally, the pain of phlebotomizing and the pain at the first moment the needle touches the skin during anaesthesia will be used as the reference and baseline for the pain assessment (form 1). During the biopsy, the external manifestations of pain will be measured *via* form 2 (Figure 5), and the blood pressure, heart rate and breathing rate will be recorded by a multi-parameter monitor. The site of needle core will be reported, because the targeted cores of the anterior zone might be associated with more pain in comparison with those of the peripheric zone (19). Before the participant is dismissed, the anaesthesia satisfaction assessment will be collected *via* form 3 (Figure 6). The pathologic data will be collected within 2 weeks after the biopsy. All of these data will be entered into a particular database. An independent monitor from the APROPOS operation group will check the quality of the data at least twice a week. The monitor may pose queries to the data, and the validity of the data will not be confirmed unless the questions have been resolved.

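### The two cancer detection outcomes are assigned a crude chi-square test, although MRI lesion status, known before the biopsy, could be used to gain some precision and protect against chance imbalance

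*Protocol article*

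**What the plan says.** The Outcomes section of the protocol article lists seven main secondary outcomes. Two are proportions of men biopsied: "The detection rate for prostate cancer, defined as the proportion of men with prostate cancer among those who undergo a prostate biopsy", and the corresponding rate for ISUP grade 2 or higher. The Statistical Analysis section fixes the method: "The secondary outcomes will be analysed with Pearson chi-square tests and expressed with 95% CIs". It names no stratum or covariate for these outcomes. The only adjustment in that section belongs to the model for the NRS pain score, in which "the imbalanced baseline characteristic will be considered the covariate, and the centre will be considered a random effect".

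The Prostate Biopsy section gives every man 12 systematic cores and adds targeted cores "only when there is at least one suspicious lesion", meaning PI-RADS 3 or higher on MRI. Table 1 places MRI and PSA at Visit 1, ahead of the block and the biopsy. The Randomisation section says that men are "allocated at a ratio of 1:1 to the perineal nerve block arm or periprostatic block arm by using block randomisation" and states no stratification factor.

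**The concern.** Each arm mixes two groups of men who can be told apart before treatment. Those with a suspicious lesion are more likely to have cancer and are also sampled more intensively. Those without one get the systematic cores only. The block cannot influence the Visit 1 MRI, so lesion status is a legitimate baseline covariate and probably a strong predictor of both detection outcomes.

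The crude comparison does not use it, which has two consequences. The confidence interval is wider than the collected data require. And if one arm happens to contain more lesion-positive men, the crude difference moves in that direction with no planned correction, since the adjustment rule for the NRS model is not extended to detection. An adjustment introduced after an imbalance had been seen would be post hoc.

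**Working it through.** **The plan's own figures.** The article gives no detection rate, lesion prevalence, expected difference or power for cancer detection, so there is no figure on this point to reproduce. Its sample size rests on the NRS score alone (2.0 versus 2.5, SD 1.0, 90% power, two-sided 5%). The t-test calculation gives 85.03, rounded up to the stated 86 per arm, and the article enrols 95 per arm.

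**Inputs.** From the article: 95 men per arm, allocated 1:1. Assumed, because the documents are silent: share of lesion-positive men q = 0.50–0.70; ISUP ≥2 detection p1 = 0.35–0.50 with a lesion and p0 = 0.08–0.15 without. The 95% CI is taken to be for the difference in proportions.

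**Formulas.**
- Overall rate: p = q·p1 + (1−q)·p0
- Crude variance per man: v = p(1−p)
- Within-stratum variance per man: w = q·p1(1−p1) + (1−q)·p0(1−p0)
- Share of variance removed: 1 − w/v
- Half-width: 1.96·√(2v/95) crude, 1.96·√(2w/95) stratified
- SD of the between-arm difference in lesion share: √(2q(1−q)/95)
- Shift in the crude difference: imbalance × (p1 − p0)

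**Example: q = 0.60, p1 = 0.45, p0 = 0.08.**
- p = 0.270 + 0.032 = 0.302
- v = 0.302 × 0.698 = 0.2108
- w = 0.6 × 0.2475 + 0.4 × 0.0736 = 0.1779
- Variance removed = 1 − 0.1779/0.2108 = 15.6%
- Half-width: 1.96·√(2 × 0.2108/95) = 13.1 points crude; 1.96·√(2 × 0.1779/95) = 12.0 points stratified
- v/w = 1.185, so the gain is worth about 18% more men

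**Ends of the assumed range.**

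| q | p1 | p0 | v | w | Variance removed | Half-width (points) |
|---|---|---|---|---|---|---|
| 0.7 | 0.35 | 0.15 | 0.2059 | 0.1975 | 4.1% | 12.9 to 12.6 |
| 0.5 | 0.50 | 0.08 | 0.2059 | 0.1618 | 21.4% | 12.9 to 11.4 |

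**Chance imbalance, same example.** SD = √(2 × 0.24/95) = 7.1 points. A difference of 10 points or more in either direction is 0.10/0.071 = 1.41 SD, with probability about 16%. A 10-point imbalance shifts the crude difference by 0.10 × 0.37 = 3.7 points. A 1.96-SD imbalance (13.9 points) shifts it by 5.2 points.

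**Behaviour of the tests.** Simulation used 40,000 trials per scenario with 95 per arm and no true effect. The scenarios (q; p1; p0) were assumed and have higher detection than the example above. The stratified test is Cochran-Mantel-Haenszel. The last two columns cover only trials with an imbalance of at least 10 points.

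| Scenario | Chi-square, all trials | Stratified, all trials | Chi-square, imbalanced | Stratified, imbalanced |
|---|---|---|---|---|
| 0.5; 0.50; 0.25 | 5.1% | 5.1% | 6.7% | 5.1% |
| 0.6; 0.60; 0.20 | 4.8% | 4.9% | 10.3% | 5.2% |
| 0.6; 0.70; 0.20 | 4.9% | 4.8% | 11.6% | 4.3% |

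In the same scenarios, power for a true 15-point difference rises from 54–55% with the chi-square to 58–68% with the stratified test.

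**The case against.** The strongest reply is that nothing here is wrong. A chi-square test suits a proportion. Under randomisation the crude comparison is unbiased, and chance imbalance in lesion status is already part of its standard error and its 5% error rate. The raised false-positive rate appears only when one conditions on a sizeable imbalance. Most of the noise is binomial and stays after stratification: 79–96% of the variance over the assumed range. All of this stands, and it limits the point to efficiency and conditional protection.

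A reader might go further and infer that imbalance in lesion status would decide the detection comparison. The figures do not support that. In the example, a 10-point imbalance moves the estimate by 3.7 points against a half-width of 13.1, and even a 1.96-SD imbalance moves it by 5.2. A reader might also infer that the comparison is there to show that detection is not harmed. The article states no such purpose and no margin; its stated objectives concern pain.

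It can also be said that covariates for unpowered secondary outcomes belong in the analysis plan, which is not shown, and that the baseline list under Data Collection and Monitoring does not mention MRI. The first would carry weight if the article were silent, but it names the test. On the second, Table 1 schedules the MRI and the targeting rule requires a PI-RADS reading before the biopsy, so the value will exist.

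**Conclusion.** The point holds as a modest, nearly free improvement. The article fixes a crude test for two outcomes whose likely strongest predictor is available before treatment, changes the sampling and is not a stated stratification factor. Under the assumed rates, stratifying removes about 4–21% of the variance, which narrows the 95% CI by between roughly 0.3 and 1.5 points on a half-width of about 13, and it largely removes the effect of a chance imbalance in lesion status. Every size rests on assumed prevalence and detection rates. That lesion status predicts cancer is implied by the article's term for the lesion and by the extra cores, but the article does not quantify it. The planned test is not invalid, the comparison is secondary and unpowered, and neither the primary pain analysis nor the sample size is affected.

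**What to change.** In the Statistical Analysis section, separate the two detection outcomes from the general chi-square sentence. State that their main analysis is a Mantel-Haenszel risk difference with 95% CI, stratified by PI-RADS ≥3 lesion on the Visit 1 MRI (yes/no), with the crude detection rates by arm reported beside it. Add lesion status to the baseline items listed under Data Collection and Monitoring, so that the stratum is recorded from the pre-biopsy reading.

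The cost is one sentence of analysis text and one entry in the baseline list. No new examination, extra patient or change to any procedure is needed. The change should be made before unblinded data are seen.

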
## Methods and Analysis

### Patient Population

Patients who fulfil all items of the inclusion criteria and exclusion criteria will be considered qualified to register for this trial. The inclusion criteria include an age between 18 and 80 years old, a PSA level of 4–20 ng/ml, and/or suspicious rectal examination findings. Volunteers will not be recruited if they have a history of an allergy to the study drug, symptomatic acute/chronic prostatitis or contraindications for a biopsy.

### Randomisation

The participants who meet the criteria and sign the consent form will be allocated at a ratio of 1:1 to the perineal nerve block arm or periprostatic block arm by using block randomisation. The random sequence will be generated by the PROC PLAN statement of the SAS program and then sealed in envelopes. The randomised number will be known and kept by one research nurse and blinded to the others. The randomised number will be revealed to the urologist (the one who will perform anaesthesia) only when the participant has already entered the operation room for anaesthesia and the prostate biopsy.

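### MRI lesion status decides who has extra targeted cores and may affect worst pain, but the primary model would adjust for it only if found imbalanced; it should be a prespecified covariate

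*Protocol article*

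**What the plan says.** Under Patient Population, eligibility rests on age, PSA and rectal examination; there is no MRI criterion. Under Prostate Biopsy, "All patients will undergo a 12-core systematic transperineal prostate biopsy with or without a targeted biopsy". The targeted part, by cognitive fusion, is done "only when there is at least one suspicious lesion" on MRI, defined as PI-RADS 3 or higher. Table 1 schedules MRI and randomisation at the same visit, Visit 1.

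Under Randomisation, participants are "allocated at a ratio of 1:1 to the perineal nerve block arm or periprostatic block arm by using block randomisation". On mechanics the section adds: "The random sequence will be generated by the PROC PLAN statement of the SAS program and then sealed in envelopes". Neither sentence names a stratification factor.

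The primary outcome is the worst pain during the biopsy on a 0–10 NRS. For the primary model, Statistical Analysis says that "the imbalanced baseline characteristic will be considered the covariate, and the centre will be considered a random effect". Lesion status is not named there. Data Collection and Monitoring has the site of each core recorded because "the targeted cores of the anterior zone might be associated with more pain in comparison with those of the peripheric zone".

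**The concern.** Two procedures are analysed as one, and a finding made before treatment decides which of them a man has. The endpoint is a maximum over the procedure. With the 12 systematic cores held fixed, adding cores to the same man can leave that maximum where it is or raise it, but cannot lower it. Lesion status is therefore a reasonable candidate for a prognostic factor, and the trial already schedules the MRI.

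The plan would use it only through a rule that looks at the observed balance first. That has two weaknesses. The model then depends on the data rather than being fixed in advance. And when the arms happen to be balanced, the covariate stays out and the variance it could explain remains in the error term. At stake are some precision and protection against an unlucky split, in a trial planned around a difference of only 0.5 NRS points.

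**Working it through.** **1. The plan's own figure.** Inputs from Sample Size: means 2.0 and 2.5 (difference 0.5), SD 1.0 in each arm, two-sided α 5%, power 90%, ratio 1:1.
- Normal approximation: n = 2(1.960 + 1.282)² × 1.0² / 0.5² = 84.1, so 85 per arm.
- Two-sample t-test: 85.03, so 86 per arm, which matches the stated figure.
- Loss of 10%: 86 × 1.1 = 94.6, so 95 per arm and 190 in total, as stated. (Dividing by 0.9 gives 96 per arm and 192; the gap is immaterial here.)
- Power with 86 per arm (normal approximation): standard error √(2/86) = 0.152; 0.5/0.152 − 1.96 = 1.32; power 90.6%.

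**2. Assumptions.** The documents do not give the share p of men with targeted cores, or the rise g in worst NRS that goes with them. I take p from 0.3 to 0.7 and g from 0.25 to 1.0 points. The top of that range for g is twice the planned treatment difference, so it is a generous upper value.

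**3. Chance imbalance without stratification, 86 per arm.** The SD of the difference in proportions is √(2p(1−p)/86).
- p = 0.3 or 0.7: √(0.42/86) = 0.070; 95% limit 1.96 × 0.070 = 0.137.
- p = 0.5: √(0.50/86) = 0.076; 95% limit 0.149.
- The probability of an imbalance above 10 percentage points is 15% to 19%.

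**4. Shift and power.** The shift in an unadjusted contrast at the 95% limit is that limit × g. If the planning SD of 1.0 is the total SD, the residual SD after adjustment is √(1 − g²p(1−p)). If 1.0 is instead the within-stratum SD, the unadjusted total SD is √(1 + g²p(1−p)). Power is Φ(0.5/(SD × √(2/86)) − 1.96).

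| p | g | Shift at 95% limit | Residual SD | Power, adjusted (1.0 is total SD) | Total SD | Power, unadjusted (1.0 is within-stratum SD) |
|---|---|---|---|---|---|---|
| 0.3 or 0.7 | 0.25 | 0.034 | 0.993 | 91.0% | 1.007 | 90.3% |
| 0.3 or 0.7 | 0.5 | 0.068 | 0.973 | 92.0% | 1.026 | 89.2% |
| 0.3 or 0.7 | 1.0 | 0.137 | 0.889 | 95.8% | 1.100 | 84.6% |
| 0.5 | 0.25 | 0.037 | 0.992 | 91.1% | 1.008 | 90.2% |
| 0.5 | 0.5 | 0.075 | 0.968 | 92.3% | 1.031 | 88.9% |
| 0.5 | 1.0 | 0.149 | 0.866 | 96.6% | 1.118 | 83.5% |

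The shift runs from 0.034/0.5 = 7% to 0.149/0.5 = 30% of the planned difference. Adjustment needs no extra men.

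**The case against.** The strongest reply is that nothing is wrong with the inference as planned. Under 1:1 randomisation an unbalanced prognostic factor causes no systematic bias. If the SD of 1.0 is a total SD, chance imbalance is already inside the standard error of 0.152 (95% margin about ±0.30), so type I error and the planned power hold. Adjustment then brings only an optional gain, and at g = 0.25 it is under one percentage point of power. All of this stands, and it limits the point to efficiency and robustness.

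A reader might infer several stronger things that the documents do not support:
- **That the protocol itself says targeted biopsy hurts more.** It does not. Data Collection and Monitoring compares anterior with peripheral sites among targeted cores, and says only that they might differ. A yes/no lesion factor does not capture site. The case for lesion status rests on the endpoint being a maximum, which gives a direction but no size; the increment could be close to zero.
- **That the factor is left wholly to chance.** Statistical Analysis does allow adjustment for an imbalanced baseline characteristic. That is a partial safeguard.
- **That lesion status would escape a baseline comparison** because it is missing from the variables named in Data Collection and Monitoring. That list is introduced as examples, and MRI has its own Visit 1 row in Table 1.
- **That the absence of strata is a proven design fault.** The document is a condensed article, and the full protocol or analysis plan may name strata. The imbalance-triggered rule is different, because the article states it outright.

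Re-stratifying is also hard to defend now. Trial Status gives 13 August 2020 as the start of recruitment, so new lists would change allocation during the trial, and extra envelope sets opened on the spot add scope for error.

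**Conclusion.** The point holds as a modest one about the primary model. Lesion status is fixed before treatment, is scheduled for collection, and can plausibly affect a worst-pain endpoint. Adjusting for it only when it looks imbalanced is weaker than adjusting for it always. There is no bias, and the stated 86 per arm and 190 in total are not called into question.

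The size depends entirely on the assumed p and g. At the unlucky 1-in-20 limit the unadjusted contrast moves by 0.03–0.15 NRS points. Power after adjustment is 91–97% instead of 90.6% if the SD of 1.0 is total. If 1.0 is within-stratum, leaving the factor out takes power to about 84–90%. The low end of each range is negligible; the high end needs targeted cores to raise worst pain by a full point.

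**What to change.** In Statistical Analysis, before unblinding, name MRI lesion status (PI-RADS 3 or higher, targeted biopsy indicated: yes/no) as a fixed covariate in the primary mixed model, included whether or not the arms differ on it. For this factor, that replaces the imbalance-triggered choice. Use the indication from the MRI rather than the cores actually taken, so that the covariate stays a pre-treatment variable. Code a man without an MRI result as no, since targeting depends on a lesion seen on MRI.

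Stratifying the randomisation by the same factor is optional, and practical only if allocation lists are still open.

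The cost is one extra model term. No additional patients, visits or procedures are needed.

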## Trial Design

In this prospective, multicentre, randomised controlled trial, we anticipate to enrol 190 patients who are scheduled to undergo a transperineal prostate biopsy. The participants will be randomised to the perineal nerve block or periprostatic block groups.

The trial flow chart is shown in Figure 1, and the details and timeframe are shown in Table 1. The primary objective of this study is to assess the efficacy of the perineal nerve block compared with that of the periprostatic block in relieving pain.

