### Sample Size

The prospective data in our previous study showed a mean maximal VAS score of 1.8 for patients who underwent a biopsy with a perineal nerve block and a mean maximal VAS score of 3.4 for those who received a periprostatic block. The standard eviations for these two methods were 1.02 and 0.96, respectively.

For the calculation of sample size, using a power of 90%, a two-sided α of 5%, and an allocation ratio of 1:1 and assuming an NRS score for the perineal nerve block of 2.0, an NRS score for the periprostatic block of 2.5, and the standard deviations for these two methods are equal to 1.0, 86 men per arm will be required. Accounting for a withdrawal/loss rate of 10%, a total of 190 participants are required for inclusion.

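### Centre is in the primary model but in neither the described randomisation nor the secondary tests; this costs some precision, not validity

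*Protocol article*

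**What the plan says.** The Trial Design section opens: "In this prospective, multicentre, randomised controlled trial, we anticipate to enrol 190 patients". The number of centres is not stated.

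The Randomisation section says that participants are "allocated at a ratio of 1:1 to the perineal nerve block arm or periprostatic block arm by using block randomisation". On generation and custody it says: "The random sequence will be generated by the PROC PLAN statement of the SAS program and then sealed in envelopes", and "The randomised number will be known and kept by one research nurse and blinded to the others". It gives no stratification factor and no block size. It does not say whether there is one list for the trial or one per centre.

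For the primary outcome, the Statistical Analysis section specifies a generalised linear mixed model in which "the centre will be considered a random effect". The next paragraph of that section reads: "The secondary outcomes will be analysed with Pearson chi-square tests and expressed with 95% CIs". It mentions no centre term. The secondary outcomes listed under Outcomes include pain at 1, 6 and 24 hours, vital-sign changes, external signs of pain, satisfaction, cancer detection and adverse events.

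**The concern.** The plan treats centre in two ways. Putting it in the primary model implies that pain scores may differ by centre. The secondary analyses then ignore it, although they include pain measured on the same scale, and the randomisation text does not name it.

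Three things are at stake:

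- **Balance.** If blocks are not formed within centre, they balance the overall total but leave the split inside each centre partly to chance.
- **Precision.** An analysis that leaves out centre keeps between-centre variation in the error term.
- **Consistency across centres.** The Introduction and Discussion give generalisability as a reason for the multicentre design. Any look at whether the effect holds across centres is easier when the arms are balanced inside each one.

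**Working it through.** **Inputs from the Sample Size section:** difference 2.5 − 2.0 = 0.5, SD 1.0, power 90%, two-sided 5%, 86 per arm, 10% loss, N = 190.

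**Assumptions, not in the document:** 3, 5, 8 or 10 centres of roughly equal size; blocks of 4; for binary outcomes an event rate near 40% and a between-centre SD of 0.8 or 0.4 on the logit scale.

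**1. The plan's own figure.** A two-sample t-test with standardised difference 0.5 needs 85.03 per arm, so 86; power at 86 is 90.3%. The allowance for loss gives 172 × 1.1 = 189.2 or 172 / 0.9 = 191.1, so 190 reproduces within rounding.

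**2. Imbalance within a centre if all centres share one list in order of arrival.** Let D be the arm difference in a centre with share p = 1/C of the patients. Allocations in the same block are negatively correlated. Summing over blocks gives Var(D) = N·p·(1 − p), in which the block size cancels. The mean absolute difference is about √(2·Var(D)/π).

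| Centres | Var(D) | Mean \|D\|, formula | Mean \|D\|, simulated |
|---|---|---|---|
| 3 | 190 × 1/3 × 2/3 = 42.2 | 5.2 | 5.17 |
| 5 | 190 × 1/5 × 4/5 = 30.4 | 4.4 | 4.38 |
| 8 | 190 × 1/8 × 7/8 = 20.8 | 3.6 | 3.62 |

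With blocks formed within centre, the simulated mean is about 0.7. The simulated chance that at least one centre ends at 60:40 or worse on a shared list is about 15%, 63% and 97% for 3, 5 and 10 centres.

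**3. Effect on the primary analysis.** Within-centre information relative to perfect balance is Σ(nA·nB/n) / (N/4). Its expected value under the shared list is 1 − (C − 1)/N.

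- 3 centres: 1 − 2/190 = 98.9%; power at 86 × 0.989 per arm is 90.0%.
- 5 centres: 1 − 4/190 = 97.9%; power 89.7%.
- 10 centres: 1 − 9/190 = 95.3%; power 88.9%.

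The largest loss is 90.3 − 88.9 = 1.4 points.

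**4. Level of the unadjusted chi-square test.** Null simulation, N = 190, logit SD 0.8, 20,000 runs per setting:

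| Centres | Unstratified list | Blocks within centre |
|---|---|---|
| 3 | 4.85% | 4.0% |
| 5 | 4.85% | 3.9% |
| 8 | 4.74% | 3.9% |

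A separate simulation gave 4.8% to 5.1% and 3.8% to 4.4%. The unstratified list keeps the nominal level. With blocks within centre, the observed difference varies less than the unadjusted standard error allows for, so the test is conservative.

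**5. Gain from accounting for centre in a binary secondary outcome.** A centre-stratified test gains about 3 points of power at logit SD 0.8 and none to 1 point at SD 0.4. It also restores the nominal level when blocks are formed within centre.

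**6. Illustration for a continuous secondary outcome.** If the centre SD is 0.5 of the within-centre SD, the variance without a centre term is 1 + 0.5² = 1.25 times as large. An effect with 90.3% power at 86 per arm then has standardised size 0.5/√1.25 = 0.447, and power of about 83%. The ratio of 0.5 is assumed.

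**The case against.** A reader might infer more than the document supports, in three ways.

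**That one trial-wide list is used.** The singular wording about the sequence and the nurse suggests this but does not state it, and a condensed article may leave such detail to the full protocol. The logistics also count against a shared list. Under Preparation Before the Block, a nurse opens a sealed envelope on the spot, and no central telephone or web system is described. Envelope sets held at each centre are at least as workable. If one list is cut into consecutive runs per centre, simulation gives a 0% chance of any centre at 60:40 or worse, and information of 99.97%, 99.9% and 99.5% of the maximum for 3, 5 and 10 centres. The imbalance figures therefore depend on an undocumented mechanism. This objection stands.

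**That centre is confounded with treatment.** Randomisation makes arm independent of centre in expectation, and the test's error rate already covers chance imbalance. The simulated level confirms this. This objection also stands.

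**That the primary result is at risk.** It is not: centre is in that model, and the power loss is small even at ten centres. The loss shown is an upper bound, because a random centre effect recovers some between-centre information.

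It can also be said that unadjusted secondary tests are common and that covariate detail often sits in an analysis plan. That has less force here, because the article does fix a method for the secondary outcomes, and that method has no centre term while the primary model has one.

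**Conclusion.** The point holds as one of efficiency and consistency. The article names no stratification by centre, adjusts the primary outcome for centre, and specifies secondary tests that ignore it. Nothing here biases a comparison or inflates type I error.

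The secondary analysis is worth changing under either reading of the randomisation. With an unstratified list, adjustment recovers precision. With blocks inside centres, it also corrects a test that runs at about 4% in place of 5%. The benefit is modest: about 3 points of power for a binary outcome when centres differ strongly, and close to nothing when they differ little. The larger figure for a continuous outcome rests on an assumed centre SD.

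The case for per-centre blocks is weaker, since they may already be in use. All sizes depend on the number of centres, the block size, the way envelopes are distributed and the centre variation, none of which the document gives.

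**What to change.** **Statistical Analysis section.** Account for centre in the secondary analyses as in the primary. For example, use Mantel-Haenszel risk differences stratified by centre, with 95% confidence intervals, for cancer detection and adverse events. Use the mixed model with centre as a random effect for the later pain scores and the other scales.

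**Randomisation section.** State whether blocks are formed within centre. If the allocation lists can still be set, generate permuted blocks separately for each centre, with varying block sizes, and hold a numbered envelope set for each centre. If recruitment has gone too far for that, describe what was done and change only the analysis.

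**Cost.** No extra patients; a little more analysis work and a sentence or two in each section. If lists are changed, one more factor is needed in sequence generation. The drawback is that blocks within a centre are easier to guess, which is why block sizes should vary.
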